#### Telerehabilitation

Remotely supervised telerehabilitation at home will be conducted twice a week for 8 weeks, in groups of 4–6 participants at a time, supervised by an experienced physiotherapist. Exercise training will comprise 30 min of lower limb aerobic training and individualised strength training exercises. Participants will undertake a total of 30 min of cycle training, in two or more bouts, in each telerehabilitation session. Cycle ergometer intensity for telerehabilitation participants will be set with the same parameters as for centre-based participants, that is, at the work rate equivalent to 60% of the peak oxygen uptake (VO_2_) on a cardiopulmonary exercise test (CPET) [34]. Intensity of cycle training will be progressed each week by 5–10% of the initial workload as tolerated [35], based on patient symptoms. Resistance training for the arms and legs will utilise equipment readily available in the home environment (e.g. sit to stand from a standard height chair, bags of rice for upper limb weights). Resistance training will be initially prescribed as tolerated, to achieve 8–12 repetitions for 3 sets of each exercise. Similar to the centre-based group, telerehabilitation participants will also be encouraged to perform an additional 3 unsupervised sessions each week, which will be documented in a home diary that is reviewed weekly by the supervising physiotherapist.

The telerehabilitation set-up will be based on our successfully piloted model [28] using readily available equipment. It will comprise a step-through exercise bike to maximise safety (Bodyworkx A915); a tablet computer (iPad – for relative ease of use and limited need to negotiate menu functions) fixed to a stand for videoconferencing; and a pulse oximeter (Nonin Palmsat 2500A; Nonin Medical Inc., Plymouth, Minnesota, USA) to monitor SpO_2_ and heart rate during training and at rest. The oximeter will not use Bluetooth but will be positioned such that the display is visible to the supervising physiotherapist throughout the session. Videoconferencing will be via Zoom videoconferencing software (San Jose, California, USA) that enables all participants to see and speak to each other. To ensure safety and understanding of equipment operation and the exercise program, the initial training session and establishment of the home exercise program will occur during a home visit by a physiotherapist.

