### Economic evaluation

Economic evaluation will take a societal perspective [54]. Economic evaluation will incorporate costs for all stakeholders involved, including participants’ out-of-pocket costs associated with health care services, and the costs of health services, including intervention costs. To facilitate documentation of personal health care costs, participants will be contacted by telephone every month during the 12-month follow-up period to document self-reported health care utilisation and to encourage completion of the monthly diary. Individual-level data for outcomes of Quality-Adjusted Life Years (QALYs), CRQ-D scores and costs will be compared to assess the incremental impact of telerehabilitation compared to traditional centre-based pulmonary rehabilitation. To compare differences in costs with differences in QALYs the SF6D score, which determines an individual’s self-valuation of health state at a specific time-point and is generated from the SF36-v2, will be converted into QALYs [55]. In addition, a separate assessment of cost effectiveness will also be undertaken by comparing the change in CRQ-D scores from baseline to end rehabilitation to the incremental costs of the intervention.

Direct costs of telerehabilitation may be higher than those for centre-based pulmonary rehabilitation, due to capital expenditure for equipment, but these may be accompanied by savings in the form of averted expenditure on health service use. Thus we will also calculate the (internal) rate of monetary return from investing in the intervention, which compares the difference in costs of health service use associated with telerehabilitation and centre-based rehabilitation to initial outlay for infrastructure [30]. For this purpose, any savings from lowering health system costs will be assessed over a time horizon of 12-months [30]. Sensitivity analyses will capture variations in cost of establishing telerehabilitation in rural versus urban settings in Australia.

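### The rate of return sets reusable equipment against only 12 months of savings, so it understates the return if net savings are positive and recur with later users

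*Protocol article*

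**What the plan says.** The Economic evaluation section expects that "Direct costs of telerehabilitation may be higher than those for centre-based pulmonary rehabilitation, due to capital expenditure for equipment", and that lower health-service use may offset this. It therefore adds an internal rate of return, which "compares the difference in costs of health service use associated with telerehabilitation and centre-based rehabilitation to initial outlay for infrastructure". For that calculation, "any savings from lowering health system costs will be assessed over a time horizon of 12-months".

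The horizon equals the period over which costs are observed: "participants will be contacted by telephone every month during the 12-month follow-up period". The one sensitivity analysis that the section names varies set-up cost between rural and urban settings.

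The Telerehabilitation section describes the equipment: "It will comprise a step-through exercise bike to maximise safety (Bodyworkx A915); a tablet computer" on a stand, and a pulse oximeter. One course of use is short: "Remotely supervised telerehabilitation at home will be conducted twice a week for 8 weeks". The article states no purchase price, useful life, residual value or re-issue rule.

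**The concern.** An internal rate of return is meant to show whether an investment pays for itself. Here the investment is equipment that the article itself calls capital, but the savings that can repay it stop at 12 months. A bike, a tablet and an oximeter issued for an 8-week course can plausibly go to someone else afterwards and still be working a year later. Any saving that later users generate with the same set falls outside the calculation.

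The article's Background calls cost analysis critical to deciding whether the model is economically viable in practice. A health service reading a negative rate of return could conclude that the equipment does not pay, when the figure shows only that it did not pay within one year.

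**Working it through.** **Nothing to reproduce.** The article gives no figure for the outlay, the savings or the rate of return. What follows shows the mechanism on assumed values.

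**Inputs from the article**
- Savings horizon: 12 months (Economic evaluation).
- Course length: 8 weeks (Telerehabilitation).

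**Assumed inputs, not in the article**
- Outlay scaled to 1.
- Annual net savings *s*, as a share of the outlay, constant from year to year: 0.25 to 1.2.
- Useful life *L*: 1, 2, 3 or 5 years, with no residual value.

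**Step 1: return by horizon.** Solve for *r* in

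0 = -1 + Σ (t = 1 to L) s / (1 + r)^t

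With L = 1 this reduces to r = s - 1, so any saving below 100% of the outlay gives a negative return.

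| s | 1 year | 2 years | 3 years | 5 years |
|---|---|---|---|---|
| 0.25 | -75% | -36% | -13% | +8% |
| 0.50 | -50% | 0% | +23% | +41% |
| 0.80 | -20% | +38% | +61% | +75% |
| 1.20 | +20% | +85% | +106% | +118% |

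Check of one cell (s = 0.5, L = 3, r = 0.234): 0.405 + 0.328 + 0.266 = 0.999, which equals the outlay of 1 up to rounding.

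The undiscounted break-even saving per year is 1/L of the outlay: 100%, 50%, 33% and 20% for 1, 2, 3 and 5 years.

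**Step 2: savings that are not positive.** With s = -0.2 the undiscounted total is -1.20 over 1 year (-0.2 - 1) and -2.00 over 5 years (5 × -0.2 - 1). With s = 0 it is -1 at every horizon. A longer horizon helps only when s is above zero.

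**Step 3: sharing a set within the year.** 52/8 = 6.5, so one set could serve at most 6 full courses a year, ignoring turnaround. If *m* users share a set, each user's 12-month saving must reach 1/m of its price to break even: 100%, 50%, 33% or 17% for m = 1, 2, 3 or 6. How the outlay is apportioned therefore moves the break-even up to six-fold, even before any question of a longer horizon.

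**Step 4: equivalent annual cost.** The factor d / (1 - (1 + d)^-L) at discount rates *d* of 3% and 5% (assumed) is 0.354 and 0.367 of the outlay for 3 years, and 0.218 and 0.231 for 5 years. These factors suit an intervention cost per participant. They do not belong inside an internal rate of return, because they already presuppose a discount rate.

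**The case against.** The strongest reply is that 12 months is simply how long each participant is followed for costs. On that reading, successive users of one set could each contribute 12 months of savings against a shared outlay, and much of the mismatch disappears. Limiting savings to what is observed is also a defensible, conservative choice, since anything longer needs extrapolation. Finally, a journal article may leave apportionment and annuitisation to the full economic plan.

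Much of this stands. A reader might infer that the whole price of a set is charged to one user or one year, and that later users are excluded. The article says neither. For the same reason, the reciprocals of the factors in Step 4 (1/0.367 = 2.7 to 1/0.218 = 4.6) should not be read as the amount by which the break-even saving is overstated: they assume full charging to one year and a 3- to 5-year life, and neither is in the document. Nor does the article say that the rural and urban comparison is the only sensitivity analysis planned.

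What remains does not rest on silence. The text fixes the initial outlay on one side and ties the 12-month limit on savings to this calculation on the other. Even if 12 months means each participant's follow-up, equipment still in service afterwards earns no credit.

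**Conclusion.** The point holds as a conditional one. If net savings are positive and would recur with later users, the planned 12-month return understates the return on the equipment. If they are zero or negative, it does not. The direction follows from the stated calculation together with a reasonable inference, not a stated fact, that the equipment is durable and can be re-issued. The size cannot be fixed from the article; the table shows only that the sign can change with the horizon, for example from -50% to +23% when annual savings are half the outlay and the life is 3 years.

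A reader might go further and conclude that 12 months is too short for the trial's whole cost question, or that the economic evaluation is biased against telerehabilitation. The document does not support that. The rate of return is an additional analysis, and the QALY and CRQ-D comparisons are separate and are not described as using it. This is a worthwhile, inexpensive improvement rather than a flaw in the main economic evaluation.

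**What to change.** - Keep the calculation on savings observed over 12 months, and label it a 12-month return and the conservative case.
- State how the outlay is apportioned over the participants each set serves.
- Add to the planned sensitivity analyses a rate of return projected over a stated range of equipment lives (for example 1 to 5 years) and of users per set, and make explicit what savings are assumed for later users.
- Do not compute the internal rate of return on a cost that has already been annuitised. Use the equivalent annual cost only for the intervention cost per participant.

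The cost is a little more economic analysis and no new patient data. The drawback is that the projected returns rest on assumptions extrapolated beyond the observed 12 months, so they should be reported beside the 12-month figure and not in place of it.

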### Statistical analysis

#### Sample size

If there is truly no difference in the change in the dyspnea domain of the CRQ between telerehabilitation or traditional centre-based pulmonary rehabilitation at the end of the 8 week intervention, then 128 participants (64 in each group) are required to be 80% sure that the 95% confidence interval will exclude a difference in means of 2.5 points or more. This is the minimal important difference (MID) for the CRQ-D [56] and assumes a standard deviation of the change in CRQ-D of 4.8 points [57]. A total of 142 participants will be randomised to allow for 10% attrition. It is anticipated that recruitment will be evenly distributed across sites.

This sample size will also give sufficient power for secondary outcomes:*6-min walk distance (6MWD)*: if there is truly no difference in 6MWD at the completion of 8-weeks of centre-based pulmonary rehabilitation or telerehabilitation, a total of 108 participants will be required to ensure that the 95% confidence interval excludes a difference in group means of 30 m or more [43], assuming a standard deviation of change in 6MWD of 53 m [58].*Endurance Cycle Time****:*** if there is truly no difference between telerehabilitation and centre-based pulmonary rehabilitation in change in constant work rate endurance time on cycle ergometer, then 52 participants are required to be 80% sure that the 95% confidence interval will exclude a difference in means of 150 s or more. This is the MID for endurance time for patients with COPD [59] and assumes a standard deviation of 184 s [59].*Pulmonary rehabilitation adherence (program completion):* data from our centres indicate that only 65% people who are referred to pulmonary rehabilitation take up the referral and complete the program. Previous studies have documented completion rates for telerehabilitation programs of over 90% [23, 60]. Using a conservative estimate of 85% completion, 128 patients will be required to detect a difference in completion rates between telerehabilitation and traditional pulmonary rehabilitation.

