## Methods

### Design

A randomised, controlled, assessor-blinded equivalence trial with an embedded economic evaluation will be conducted at two centres in metropolitan Melbourne (Alfred Health and Austin Health), and one regional centre (Wimmera Health Care Group, Horsham), Australia. Both regional and metropolitan sites have been included to increase the external validity of our model. The study was approved by the Human Research Ethics Committee at Alfred Health for all sites, and local governance approvals obtained from all participating sites (Austin Health, Wimmera Health Care Group and West Wimmera Health Service). The trial was registered at anzctr.org.au (ACTRN12616000360415) on March 21, 2016.

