#### Analysis

Continuous variables will be analysed by fitting linear mixed models, controlling for recruitment centre and baseline values as required. The proportion of participants who attend for at least 70% of the program will be compared between groups using a chi-squared test and the relative risk of non-completion will be determined. All data will be analysed by intention-to-treat. A per-protocol analysis will also be conducted to reduce the risk of Type 1 error, as recommended in the CONSORT Extension for reporting of non-inferiority and equivalence trials [61]. Alpha will be set at 0.05.

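### The stated sample sizes (128, 108, 52) fit a 90% confidence interval; under the 95% rule as written, unadjusted primary power is about 67%, not 80%

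*Protocol article*

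**What the plan says.** The Design section describes the trial in these terms: "A randomised, controlled, assessor-blinded equivalence trial with an embedded economic evaluation will be conducted at two centres". The Sample size section then fixes every input for the primary outcome:

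- True difference of zero: "If there is truly no difference in the change in the dyspnea domain of the CRQ".
- Size, power and interval: "then 128 participants (64 in each group) are required to be 80% sure that the 95% confidence interval will exclude a difference".
- Margin: "exclude a difference in means of 2.5 points or more".
- Variability: the text "assumes a standard deviation of the change in CRQ-D of 4.8 points".

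The same 95% interval is named for two secondary outcomes. For 6-minute walk distance (margin 30 m, SD 53 m), "a total of 108 participants will be required to ensure that the 95% confidence interval excludes a difference in group means". For endurance cycle time (margin 150 s, SD 184 s), "then 52 participants are required to be 80% sure that the 95% confidence interval will exclude" the margin.

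The Analysis section adds only "Alpha will be set at 0.05". It does not say whether this is 5% in total or 5% for each one-sided test, and it names no interval for the equivalence decision.

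**The concern.** A sample size tied to a named interval, margin, SD, true difference and power can be checked directly, and this one does not agree with its own inputs. Requiring a two-sided 95% interval to lie within ±2.5 is the same as two one-sided tests at 2.5% each. That rule is stricter than the one the published numbers satisfy.

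Two things are at stake. If the 95% rule is applied as published, the chance of missing true equivalence on the primary outcome is much larger than stated. If instead a 90% interval is used at analysis because it matches the numbers, equivalence is declared on a looser standard than the one published. The single alpha of 0.05 fits either reading, so the choice could remain open until the data are seen.

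**Working it through.** **Inputs** (Sample size section; 1:1 allocation from Recruitment and randomisation): margin *m* and SD of 2.5 and 4.8 (CRQ-D), 30 and 53 (6-minute walk distance), 150 and 184 (endurance cycle time); true difference 0; power 80%. The walk-distance sentence gives no power, so 80% is assumed there.

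**Formula.** For equivalence with a true difference of 0, both limits must clear the margin, so the type II error is split between the two sides:

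n per group = 2 × SD² × (z₁₋ₐ + z₀.₉₀)² / m²

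where a = 0.05 for a 90% interval and a = 0.025 for a 95% interval.

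- a = 0.05: (1.645 + 1.282)² = 8.564
- a = 0.025: (1.960 + 1.282)² = 10.507

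**Reproducing the published figures, then applying the stated rule:**

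| Outcome | 2 × SD² / m² | n per group, 90% CI | Total | n per group, 95% CI | Total | Published |
|---|---|---|---|---|---|---|
| CRQ-D | 7.373 | 63.1 | 128 | 77.5 | 156 | 128 |
| 6-minute walk distance | 6.242 | 53.5 | 108 | 65.6 | 132 | 108 |
| Endurance cycle time | 3.009 | 25.8 | 52 | 31.6 | 64 | 52 |

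All three published figures match the 90% interval exactly; none matches the 95% interval. With the t distribution the 95% totals are 158, 134 and 66.

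**Other readings tried.** A 95% interval with only one limit required to clear the margin, at 80% power, gives 116, 98 and 48. One-sided 5% non-inferiority at 80% power gives 92, 78 and 38. Neither reproduces the published set.

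**Power for CRQ-D at 64 per group under the 95% rule:**

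- SE = 4.8 × √(2/64) = 0.849
- 95% half-width = 1.96 × 0.849 = 1.66, so the observed difference must be smaller than 2.5 − 1.66 = 0.84
- Power = 2Φ(2.5/0.849 − 1.96) − 1 = 67.6%; integrating over the t distribution gives 66.5%
- Under a 90% interval the same size gives 80.7% (normal) or 80.1% (t), which is the stated 80%
- If all 142 randomised were evaluable, the 95% rule gives 74.7% (normal)
- At 128, 80% power under the 95% rule holds only for a margin of (1.960 + 1.282) × 0.849 = 2.75 points

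**Where the two intervals disagree.** At the planned SD and size, the 90% rule accepts an observed difference up to 2.5 − 1.645 × 0.849 = 1.10. Results between 0.84 and 1.10 points are equivalent under one interval and not under the other.

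**Secondary outcomes under the 95% rule (normal).** Walk distance: 67.4% at the quoted 108, 78.6% at 128. Endurance cycle time: 67.3% at the quoted 52, 99% at 128.

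**The case against.** The strongest counter-argument is that 67% describes an unadjusted comparison, while the Analysis section plans linear mixed models that control for centre and baseline where needed. Adjustment would restore 80% at 64 per group if covariates explained 1 − 64/77.47 = 17.4% of the variance in change, that is, a residual SD of about 4.36 or lower. If baseline and follow-up variances are equal, baseline explains (1 − r)/2 of that variance, where r is their correlation. The protocol gives no r. Assumed values of 0.5, 0.6, 0.7, 0.8 and 0.9 give power of 85%, 82%, 78%, 75% and 71%. So actual power is uncertain and may reach 80%. What stands is that the sample size text uses the full SD of 4.8, claims no such gain, and the adjustment is conditional.

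Second, two one-sided 5% tests are a conventional approach to equivalence and compatible with an alpha of 0.05. The slip may therefore be in the label, with 80% power intact. That is possible, but the 95% interval is written three times and no 90% interval appears anywhere, so the text needs correcting on this reading too.

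Third, keeping the 95% rule does not raise the risk of falsely claiming equivalence; the harm is lost power. That is right. The looser standard arises only if the interval is changed.

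Fourth, the secondary figures matter less. The trial will not run at 52 or 108, endurance cycle time is well powered at 128, and walk distance falls short by only one or two percentage points. These figures mainly corroborate the diagnosis.

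**Conclusion.** The point holds. The protocol's own inputs give 156, 132 and 64 under the 95% rule, not 128, 108 and 52. The published figures come from 5% per side. For the primary outcome, power under the published rule is 66.5% to 67.6% rather than 80%, and the chance of missing equivalence is about one in three rather than one in five.

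This rests on a true difference of zero, an SD of 4.8, 128 evaluable participants, both limits having to fall within ±2.5, and no gain from covariate adjustment. The interval and the numbers cannot both be right as written, and the conflict concerns the decision rule for the primary outcome, so it should be corrected before analysis.

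**What to change.** Choose one rule and state it consistently.

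1. **Keep the 95% interval (preferred, since it is the published standard).** Restate CRQ-D power as about 67% with 128 evaluable, unadjusted, with 156 needed for 80%. Change the requirement for walk distance to 132 and for endurance cycle time to 64. Add that 128 regains 80% if prespecified covariates, mainly baseline CRQ-D, explain at least 17% of the variance in change, and fix those covariates rather than leaving adjustment conditional.
2. **If two one-sided 5% tests were intended,** replace 95% with 90% in all three sentences. Because this loosens the published standard and recruitment is under way, date and justify the change before any unblinded comparison.

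In either case, replace the bare alpha in the Analysis section with the chosen interval and the ±2.5 rule for CRQ-D.

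The cost is wording in the protocol and analysis plan, and under option 1 a less favourable power statement. Neither option requires more participants. If the sponsor wishes to hold both the 95% rule and 80% unadjusted power, 156/0.9 gives about 174 randomised instead of 142; that is a separate decision.

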### Recruitment and randomisation

Participants will be randomly allocated (1:1) to traditional centre-based pulmonary rehabilitation or telerehabilitation. A computer-generated, block randomisation scheme will be used with stratification for (i) recruitment in stable state vs post hospitalisation for respiratory exacerbation; (ii) site of recruitment; and (iii) diagnosis of ILD vs other diagnoses. Sequence generation will be performed by an individual who is independent of the research team and randomisation will occur using an online database. The randomisation sequence will be concealed from investigators. Participants will be allocated to groups after completion of baseline assessment. Given the nature of the intervention (exercise training) participants will not be blinded to the intervention, however all outcomes will be measured by an independent assessor blind to group allocation. The flow of participants through the study will be reported according to the recommendations of the Consolidated Standard of Reporting Trials (CONSORT) [32].

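### The 128 given for detecting 65% vs 85% program completion gives about 75% power, not 80%, and the 65% is measured on a different population from the one the trial randomises

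*Protocol article*

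**What the plan says.** The Sample size section of the protocol article sets 128 participants for the primary outcome and 142 randomised after a 10% attrition allowance. It then claims: "This sample size will also give sufficient power for secondary outcomes". Program completion is one of the outcomes listed under that claim.

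- Control rate: "data from our centres indicate that only 65% people who are referred to pulmonary rehabilitation take up the referral and complete the program".
- Telerehabilitation rate: "Previous studies have documented completion rates for telerehabilitation programs of over 90"%, reduced to 85% as a cautious choice.
- Conclusion: "Using a conservative estimate of 85% completion, 128 patients will be required to detect a difference in completion rates".

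No power and no sidedness are given for this item. The Analysis section says that the proportion attending at least 70% of the program "will be compared between groups using a chi-squared test", that analysis is by intention-to-treat, and "Alpha will be set at 0.05". Under Participants, everyone gives written consent. Under Recruitment and randomisation: "Participants will be allocated to groups after completion of baseline assessment". The Background section lists higher completion with telerehabilitation among the study hypotheses.

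**The concern.** Two things do not fit.

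First, 128 equals the number already fixed for the primary outcome, and the usual formula for two proportions does not return it for 65% vs 85% at 80% power.

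Second, the two rates have different denominators. The 65% counts against the program every referred person who never took up the referral. The 85% is discounted from completion rates of telerehabilitation programs. The trial's own measure is attendance at 70% or more of planned sessions among people who consented, finished baseline testing (including a maximal cardiopulmonary exercise test) and were then randomised. Many who decline a referral would not get that far, so the control arm should complete at a higher rate than 65%.

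At stake is how a non-significant completion result is read. If the article says that power is adequate and it is not, such a result could be taken as evidence against an adherence advantage. The primary equivalence sample size is not affected by this point.

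**Working it through.** **Inputs.** p1 = 0.65 and p2 = 0.85 (Sample size); chi-squared test, alpha 0.05 (Analysis), taken as two-sided; 1:1 allocation (Recruitment and randomisation). Power of 80% is inferred from the dyspnea-domain and endurance-time calculations in the same section.

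**1. Can 128 be reproduced?** The pooled formula for n per group is

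n = [1.960·√(2·p̄(1−p̄)) + 0.842·√(p1(1−p1) + p2(1−p2))]² / (p2 − p1)², with p̄ = 0.75.

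The terms are 2·0.75·0.25 = 0.375 and 0.65·0.35 + 0.85·0.15 = 0.2275 + 0.1275 = 0.355. So n = (1.2002 + 0.5015)² / 0.04 = 72.4, that is 73 per group, **146 in total**.

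Other standard versions, two-sided with 80% power:

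| Method | Total N |
|---|---|
| Unpooled variance | 140 |
| Arcsine | 142 |
| Pooled | 146 |
| Single pooled variance | 148 |
| Continuity-corrected | 166 |

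None gives 128. Values at or near 128 appear only under settings that the article does not state:
- two-sided with 75% power: 130 (pooled) or 126 (arcsine);
- one-sided with 85% power: 128 (unpooled) or 130 (arcsine);
- one-sided with 80% power, already inflated for 10% dropout: 114/0.9 = 127. This does not match the article, where 128 is the number before attrition and 142 the number after (128/0.9 = 142.2).

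**2. Power at the stated rates.** Power = Φ{[0.20·√n − 1.960·√0.375] / √0.355}.

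- n = 64 per group (128): Φ(0.671) = **74.9%**; exact enumeration of the chi-squared test gives 75.8%.
- n = 71 per group (142): Φ(0.814) = **79.2%**; exact 80.4%.

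With a continuity correction or Fisher's test the exact figures are about 69% and 74%.

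**3. Effect of the denominator (illustration only).** The documents give no uptake rate. Suppose a fraction u of referred people take up, and everyone who does not is excluded before randomisation. That is the extreme case. The control completion rate in the trial is then 0.65/u. Power with all 142 (71 per group, pooled formula):

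| Assumed uptake u | Control rate 0.65/u | Telerehabilitation 85% | Telerehabilitation 90% |
|---|---|---|---|
| 95% | 68.4% | 65% | 89% |
| 90% | 72.2% | 46% | 78% |
| 85% | 76.5% | 25% | 58% |

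The 90% column is shown because the article reports documented rates above 90% and treats 85% as cautious.

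**The case against.** **The arithmetic error matters little in practice.** Attendance is a session record, so it need not be lost when an outcome assessment is missed, and intention-to-treat can include all 142. At the article's own rates that gives 79–80% power. This stands: on the arithmetic alone the adequacy claim is nearly met, and what is wrong is the 128.

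**The 80% two-sided target is inferred.** No power is stated for this outcome and the hypothesis is directional; one-sided at 5%, 64 per group would give 84% power. It is right that the target is an inference. But a chi-squared test at 0.05 is normally two-sided and the article does not announce a one-sided test, so this does not rescue the 128.

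**A reader might infer that the true power is far below adequate.** The documents do not support that. The uptake rates in the illustration are assumed, and the answer depends heavily on the telerehabilitation rate: at 90% the power with 142 remains 78% or more for uptake of 90% or higher.

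**A reader might also infer that people who do not take up are never randomised.** That is too strong. Allocation follows baseline assessment, so someone allocated to the centre can still fail to start. The Background section names travel, transport and disability as barriers, and consent does not remove these. Under intention-to-treat such people count as non-completers. Dividing 65% by uptake is therefore an upper bound on the correction for the assumed uptake. Recruitment of patients admitted with an exacerbation adds doubt about how far any referral-based rate applies.

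None of this makes the two denominators equal. Calling 85% conservative protects only the telerehabilitation arm; the 65% errs in the other direction.

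**Conclusion.** The point holds in two parts.

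1. The 128 is misstated. With a two-sided 5% test and an inferred 80% power target, 146 are needed; 128 gives about 75% power and all 142 give about 79–80%. This is a modest error.
2. The 65% is uptake and completion combined among referred people, and does not describe the population that the trial randomises. The control rate is probably above 65% and the 20-point difference probably too large. The direction is reasonably clear but the size is unknown. Under the extreme-case illustration, power with 142 runs from 25% to 89% over the assumptions shown, so adequate power is neither established nor ruled out.

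This concerns a secondary outcome that carries a stated hypothesis. The power statement should be corrected, but the trial's size and its primary analysis need not change on this account.

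**What to change.** - Replace the 128 with the figure that follows from the stated rates (146 for a two-sided 5% test with 80% power), and state the power and sidedness used.
- Take the control rate from the centres' own program data: completion among people who attended a baseline assessment, with completion defined as in the trial (at least 70% of planned sessions). If those data were not tabulated, show a range of control rates.
- State the resulting power for all 142 randomised, by intention-to-treat.
- If the recomputed power is below 80%, qualify or remove the claim of sufficient power for this outcome.
- Report a risk difference with 95% confidence interval alongside the relative risk of non-completion already planned, so that a non-significant result is read with its uncertainty.

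The cost is a change of wording and, where the data exist, a look-up in existing program records. No extra patients are needed. The downside is a less favourable stated power for a secondary outcome.
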